### Measures

#### Screening

During the screening session, sleep disturbance was assessed using the Duke [41] and ISI. The Duke is a structured clinical interview that screens for sleep disorders in accordance with criteria of both the DSM-IV and the International Classification of Sleep Disorders, 2nd Edition, (ICSD-2). It is composed of 4 modules that assess sleep disorder symptoms associated with insomnia, hypersomnia, circadian rhythm sleep disorders, and sleep disorders associated with parasomnias.

The ISI is a 7-item, self-report measure of insomnia severity. The items consist of severity of early, middle, or late insomnia; sleep dissatisfaction; interference with daytime functioning; perception of sleep problems by others; and distress caused by sleep difficulties. Items are scored from 0 to 4, with 0 indicating no problem and 4 indicating a very severe problem. Score ranges for insomnia are as follows: 0-7, absent; 8-14, subthreshold; 15-21, moderate; and 22-28, severe.

We administered the MINI [45] to screen for psychosis, bipolar disorder, and substance abuse or dependence. The MINI is a structured, diagnostic interview for DSM-5 psychiatric disorders that was administered by clinically trained study staff.

Suicidal ideation and behaviors are assessed using the self-report version of the S-STS [47]. The S-STS is a 15-item questionnaire assessing the risk of suicidality using a 5-point Likert scale ranging from 0 to 4, with 0 indicating no problem and 4 indicating a very severe problem. For this study, to minimize participant burden, we omitted item 15, which asks about suicide attempts, because high-risk participants would already be identified through the distressed patient protocol (described in previous sections).

#### Primary Outcomes

Primary outcomes of insomnia, well-being, and predictors of treatment response are collected at baseline (week 0), weeks 6, 12, 28, and 56. Primary outcomes of insomnia (ISI) and well-being were also collected at weeks 1-5. The primary time points are weeks 6, 12, and 28.

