#### Power Calculation

Due to the anticipated difficulties in recruitment that will likely arise from the complexities of running a study during a pandemic and the time-sensitive nature of implementing an early sleep intervention relative to both the start of the pandemic and insomnia symptoms, we view this trial as a feasibility study. Therefore, for this feasibility trial, we aimed to recruit a total of 50 subjects, which would result in 25 subjects in each study group. With this sample size, our power calculations were derived using the 2-group *t* test of equal means based on the difference between CBT-I and waitlist control group at 28 weeks, at a 5% level of significance. With 25 per group, the study is 80% powered to detect a large effect size (Cohen d=0.80).

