##### Insomnia

The change in clinically significant insomnia symptoms (meeting criteria for insomnia disorder diagnosis) and subjective ratings of current insomnia symptoms are primary measures of insomnia. Insomnia disorder diagnosis is assessed using the Duke insomnia disorder module. Subjective sleep complaints are assessed using ISI report of current symptoms over the past 2 weeks. The Duke insomnia disorder module is only collected at weeks 0, 12, 28, and 56.

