##### Well-being

We measure change in depressive symptoms as primary outcomes of well-being. Depressive symptoms are evaluated using the Patient Health Questionnaire-9 (PHQ-9) [48]. The PHQ-9 is a self-administered, 9-item questionnaire that assesses each of the 9 DSM-IV depression criteria. The total score ranges from 1 to 27. Answers are given on a 4-point Likert scale ranging from 0 (Not at all) to 3 (Nearly every day), with higher scores reflecting increased severity of depressive symptoms.

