#### Primary Analyses

Statistical analyses aim 1 is to determine whether a brief, telehealth CBT-I reduces insomnia symptoms arising during the COVID-19 pandemic. All primary analyses will be performed using the intention-to-treat principle. We will test whether CBT-I is superior to a waitlist control in reducing insomnia symptoms by using a mixed effects linear model with autoregressive error structure using intention-to-treat analysis with outcomes at time points 6, 12, and 28. Insomnia severity as measured by the ISI will be entered as the dependent variable with randomization group (2 levels), time point (weeks 0, 6, 12, and 28), and group-by-time interaction included as fixed effects. The model will also include a random slope. Several hypotheses (1.1a-d) will be tested using the described mixed effects model.

Hypothesis 1.1a is that individuals assigned to the CBT-I group will experience an improved trajectory of insomnia symptoms during the waitlist-controlled 28-week period relative to those assigned to the waitlist control group. This hypothesis will be tested using a likelihood ratio test of the coefficients of the time and group-by-time interaction of the aforementioned mixed effects linear model.

Hypotheses 1.1b-1.1d are that individuals assigned to the CBT-I group during the waitlist-controlled period will have lower insomnia symptoms compared with those assigned to the waitlist-control group immediately posttreatment (hypothesis 1.1b; week 6) and at the short-term (hypothesis 1.1c; week 12) and long-term (hypothesis 1.1d; week 28) follow-ups. These hypotheses will be tested using the aforementioned mixed effects linear model with independent likelihood ratio tests using the treatment coefficient for the posttreatment (hypothesis 1.1b; Δ_1_ in Figure 2), short-term (hypothesis 1.1c; Δ_2_ in Figure 2), and long-term (hypothesis 1.1c; Δ_3_ in Figure 2) follow-up time points.

We will also test whether CBT-I is superior to the waitlist control in preventing an insomnia diagnosis following treatment by using multiple logistic regression analysis.

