## Results

### Trial Status and Timeline

The trial began recruitment on June 4, 2020, and the first participant was consented on June 10, 2020. As of October 2021, 794 subjects had completed prescreening, and 96 subjects had completed a Zoom screening session. A total of 49 participants were randomized to a study group (26 to the CBT-I group and 23 to the waitlist control group). Overall, 38 participants had completed the week 6 follow-up, 37 had completed the week 12 follow-up, 34 had completed the week 28 follow-up, and 15 had completed the week 56 follow-up. At the time of this writing, there were an additional 3 participants awaiting the 28-week follow-up and a total of 23 participants awaiting the week 56 follow-up (13 in CBT-I and 10 in waitlist control group). The study closed to enrollment of new subjects on June 17, 2021. As of the writing of this paper, due to the outstanding data collection of the remaining 28- and 56-week data, we had conducted interim analyses for the week 6 follow-up but had not tested the results of our primary hypotheses in full. We expect primary results of the study to be published in 2022.

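### Eight separately tested primary contrasts and no lead one: the outcome and time point that give the trial's main answer should be named

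*Protocol article*

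**What the plan says.** All references are to the protocol article.

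- **Primary Outcomes:** "The primary time points are weeks 6, 12, and 28".
- **Primary Outcomes, Insomnia:** the Duke diagnosis and the ISI share primary status; the diagnosis and "subjective ratings of current insomnia symptoms are primary measures of insomnia". The Duke module is collected at weeks 0, 12, 28 and 56, so not at week 6.
- **Primary Outcomes, Well-being:** "We measure change in depressive symptoms as primary outcomes of well-being", measured by the PHQ-9.
- **Primary Analyses, aim 1:** "We will test whether CBT-I is superior to a waitlist control in reducing insomnia symptoms". Hypotheses 1.1b–d take ISI at weeks 6, 12 and 28 "with independent likelihood ratio tests using the treatment coefficient for the posttreatment" and the two later follow-ups. Hypotheses 1.2a–b take the diagnosis at weeks 12 and 28 in two separate logistic models. Hypothesis 1.1a is a trajectory test.
- **Primary Analyses, aim 2:** hypotheses 2.2b–d repeat the three time-point tests for depression, and 2.2a is a second trajectory test. The measure entered in this model is the BDI-II, not the PHQ-9.
- **Power Calculation:** a two-group t test on the "difference between CBT-I and waitlist control group at 28 weeks, at a 5% level of significance", with 25 per group, 80% power and d = 0.80. No outcome is named.
- **Statistical Procedure and Data Analysis (opening paragraph) and Discussion:** interpretation and publications are to rest on effect sizes and confidence intervals more than on significance.

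**The concern.** The candidate contrasts can disagree. ISI may differ clearly at week 6 and no longer at week 28, or ISI may improve while depression does not. With no lead contrast, a reader of the results cannot tell which estimate answers the trial's question, and nothing in the article prevents the most favourable of eight from being given most weight. That matters here because the article says the findings will guide larger trials. The largest of several estimates from about 25 per group tends to overstate the effect, whether or not a p-value is attached. The single stated 5% level and 80% power describe one week-28 test of an unnamed outcome, not the set of tests listed under Primary Analyses.

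**Working it through.** **1. The plan's own figure.** Inputs from Power Calculation: n = 25 per group, d = 0.80, "at a 5% level of significance". Sidedness is not stated.

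- Noncentrality: 0.80 × √(25/2) = 2.83, with 48 degrees of freedom.
- Two-sided 5%: critical t = 2.01, power 0.79 (0.81 by normal approximation).
- One-sided 5%: power 0.87.

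The stated 80% is reproduced by one two-sided test, so two-sided 5% is used below.

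**2. Count of tests under Primary Analyses.**

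| Outcome | Week 6 | Week 12 | Week 28 | Contrasts |
|---|---|---|---|---|
| ISI (1.1b–d) | yes | yes | yes | 3 |
| Duke diagnosis (1.2a–b) | not collected | yes | yes | 2 |
| Depression (2.2b–d), PHQ-9 | yes | yes | yes | 3 |
| Depression (2.2b–d), if BDI-II | not collected | yes | yes | 2 |

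The total is 3 + 2 + 3 = 8 with the PHQ-9, or 3 + 2 + 2 = 7 with the BDI-II. Secondary Outcomes gives weeks 0, 12, 28 and 56 for the BDI-II; only the secondary insomnia measures and the GAD-7 are added at weeks 1–6. The trajectory tests 1.1a and 2.2a are extra.

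**3. Chance of at least one nominally significant contrast when there is no effect.** With independent tests it is 1 − 0.95^8 = 0.337 in either direction and 1 − 0.975^8 = 0.183 in favour of CBT-I. The documents give no correlation between the test statistics, so a common correlation r is assumed (multivariate normal, threshold 1.96).

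| r | 8 contrasts, either direction | 8, favouring CBT-I | 7 contrasts, either direction | 7, favouring CBT-I |
|---|---|---|---|---|
| 0 | 0.34 | 0.18 | 0.30 | 0.16 |
| 0.3 | 0.30 | 0.15 | 0.27 | 0.14 |
| 0.5 | 0.25 | 0.13 | 0.23 | 0.11 |
| 0.7 | 0.19 | 0.10 | 0.18 | 0.09 |
| 0.8 | 0.16 | 0.08 | 0.15 | 0.07 |

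The single-test values are 0.05 and 0.025.

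**4. Other correlation patterns.** Correlation was also allowed to decay over time within an outcome (0.3 to 0.8 per step), with 0.3–0.7 assumed between ISI and depression and 0.5–0.7 between ISI and the diagnosis. The eight contrasts then give 21–31% in either direction and 10–16% in favour of CBT-I. Adding a joint three-week test for ISI and another for depression, as stand-ins for the trajectory tests, moves the either-direction range to 23–32%.

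**5. Effect of the remedy.** One named contrast has a 5% two-sided error (2.5% in favour of CBT-I) and keeps power at 0.79. Keeping all eight with Bonferroni (0.05/8 = 0.00625 each) would cut power per contrast at d = 0.80 to 0.49.

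**The case against.** The strongest reply is that this is a feasibility trial whose article puts estimation ahead of significance for all analyses and publications. The 5% level is an input to the power calculation, not a stated decision rule for the hypotheses. This stands in part: the rates above are not probabilities of a declared claim. But Primary Analyses still frames aims 1 and 2 as superiority tests, and its mediation criterion requires significant paths. Estimation also needs a main estimate.

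A second reply is that two aims need not form one error family, and that alpha splits are often left to an analysis plan, which is not shown. That is fair as to adjustment. The choice of primary outcomes and time points, however, is made in the article itself, and it is left unranked.

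A third reply is that another lead is defensible. Aim 1 is worded across 28 weeks and the trajectory hypothesis comes first. That also stands: ISI at week 28 is the better fit to the power calculation, not the only possible choice.

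A reader might also infer that week-6 results were known while the primary contrasts could still be chosen, because Trial Status and Timeline says "we had conducted interim analyses for the week 6 follow-up but had not tested the results of our primary hypotheses in full". The sentence dates the article, not the choice of outcomes, and it already discloses those analyses. When the outcomes were fixed cannot be told from this document.

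**Conclusion.** The point holds as a matter of an unnamed lead contrast. Three outcomes at up to three time points are all primary and separately tested, and the one design calculation names a week but no outcome.

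If the tests are read at an unadjusted two-sided 5%, the chance of at least one nominally significant result under no effect is about 16–34% in either direction and 8–18% in favour of CBT-I, for an assumed correlation of 0.8 to 0. With seven contrasts it is 15–30% and 7–16%.

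A reader might take the 25% at a correlation of 0.5 as the probability that a chance finding is reported as superiority. The document does not support that. The figure counts results against CBT-I as well; the favourable part is about 13%, it rests on an assumed correlation, and the article does not make significance its basis for conclusions. The change should be made, but the trial does not depend on it.

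**What to change.** - **Primary Outcomes:** name one primary contrast, the CBT-I minus waitlist difference in ISI at week 28, from the aim 1 mixed model. It is the aim 1 measure at the time point the power calculation uses.
- **Power Calculation:** add *in ISI* to the difference at 28 weeks.
- **Primary Analyses:** label ISI at weeks 6 and 12, the Duke diagnosis, depression at all weeks and both trajectory tests as secondary, reported as estimates with 95% confidence intervals and no separate superiority claim. This also brings the section into line with the declared emphasis on estimation.
- **Depression measure:** reconcile the PHQ-9 in Primary Outcomes with the BDI-II in the aim 2 model, since hypothesis 2.2b needs a measure collected at week 6.

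The cost is wording only, with no further data or participants. The real downside is that the other outcomes, including the depression measure at the centre of aim 2, lose the primary label.

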##### Insomnia

The change in clinically significant insomnia symptoms (meeting criteria for insomnia disorder diagnosis) and subjective ratings of current insomnia symptoms are primary measures of insomnia. Insomnia disorder diagnosis is assessed using the Duke insomnia disorder module. Subjective sleep complaints are assessed using ISI report of current symptoms over the past 2 weeks. The Duke insomnia disorder module is only collected at weeks 0, 12, 28, and 56.

##### Well-being

We measure change in depressive symptoms as primary outcomes of well-being. Depressive symptoms are evaluated using the Patient Health Questionnaire-9 (PHQ-9) [48]. The PHQ-9 is a self-administered, 9-item questionnaire that assesses each of the 9 DSM-IV depression criteria. The total score ranges from 1 to 27. Answers are given on a 4-point Likert scale ranging from 0 (Not at all) to 3 (Nearly every day), with higher scores reflecting increased severity of depressive symptoms.

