The Beck Depression Inventory-II (BDI-II) [59,60] is used as a secondary measure of depressive symptom change over time. We will sum all items except one sleep item, and the average item score for the remaining 20 items will be multiplied by 21 (the original number of items) to create a modified depression scale that maintains the original range (ranges: 0-13, minimal; 14-19, mild; 20-28, moderate; and 29-63, severe). The BDI-II is a 21-item self-report scale with high validity and reliability that assesses the severity of depressive symptoms. The depressive items consist of sadness, pessimism, past failure, loss of pleasure, guilty feelings, punishment feelings, self-dislike, self-criticalness, suicidal thoughts or wishes, crying, agitation, loss of interest, indecision, worthlessness, loss of energy, changes in sleep pattern, irritability, changes in appetite, concentration difficulty, tiredness or fatigue, and loss of interest in sex. Items are scored from 0 to 3, and higher scores indicate greater level of severity.

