Hypotheses 1.2a and 1.2b are that individuals who were assigned to the CBT-I group will be less likely to have an insomnia diagnosis than those who were assigned to the waitlist control group at weeks 12 and 28. These hypotheses will be tested using 2 separate logistic regression models, one using the short-term (hypothesis 1.2a; 12 weeks) and one using long-term (hypothesis 1.2b; 28 weeks) follow-up insomnia diagnosis, as defined by the Duke, as the dependent variable, with treatment (CBT-I, waitlist) as the independent variable.

Statistical analyses aim 2 is to determine whether a brief, telehealth CBT-I improves well-being during the COVID-19 pandemic. We will test whether immediate CBT-I is superior to a waitlist control in improving depressive symptoms as the primary measure of well-being during the waitlist-controlled period (28-week duration) by using a mixed effects linear model with autoregressive error structure using intention-to-treat analysis. Depression severity, as assessed by the BDI-II, will be entered as the dependent variable with baseline covariates used for stratified randomization (ie, baseline insomnia severity and sex), group (immediate CBT-I or waitlist control), time point (weeks 0-6, 12, and 28), and group-by-time interaction included as fixed effects. The model will also include a random slope. Separate, secondary analyses will be conducted on the secondary measures relating to well-being described in the Secondary Outcomes section (eg, anxiety, suicidality, quality of life). Several hypotheses will be tested using this model.

Hypothesis 2.2a is that individuals assigned to the CBT-I group will have an improved trajectory of depressive symptoms across the 28 weeks relative to individuals assigned to the waitlist control group. This hypothesis will be tested using a likelihood ratio test of the coefficients of the time and group-by-time interaction terms of the aforementioned mixed effects linear model.

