Hypotheses 2.2b-2.2d are that individuals assigned to the CBT-I group will have lower depressive symptoms compared who those who were assigned to the waitlist control group immediately posttreatment (hypothesis 2.2b; week 6) and at the short-term (hypothesis 2.2c; week 12) and long-term (hypothesis 2.2d; week 28) follow-ups. These hypotheses will be tested using the aforementioned mixed effects linear model with independent likelihood ratio tests using the treatment coefficient for the posttreatment (hypothesis 1.2b; week 6), short-term (hypothesis 1.2c; week 12), and long-term (hypothesis 1.2c; week 28) follow-up time points.

Hypothesis 2.3 is that improvement in insomnia symptom severity (measured by the ISI) will mediate subsequent improvement in well-being from baseline (week 0) to posttreatment (week 6), short-term follow-up (week 12), and long-term follow-up (week 28). Using the approach described by Kraemer at al [61] and Manber et al [34], linear regression analyses will be used to determine whether change in the ISI score from Session 1 (week 1) to Session 4 (week 5) of treatment mediates the subsequent depressive symptom improvement (primary outcome measure) after the completion of treatment (week 6). Change in ISI score at Session 4 will be estimated as the slope of the regression line of ISI scores from Session 1 (week 1) through the treatment phase to Session 4 (week 6) using all available data from each participant. The model will include group (CBT-I or waitlist control), change in ISI score from Session 1 to Session 4 (participant specific slopes), and their interaction with depression severity, as measured by the PHQ-9, as the dependent variables. Mediation will be tested using the MacArthur approach as described by Kraemer et al [62]. Specifically, a mediation effect requires a significant effect of the intervention on the mediator (Path A in Figure 3) and a significant association between the mediator and the outcome (Path B in Figure 3).

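### The primary PHQ-9 keeps its sleep criterion while the secondary BDI-II drops its sleep item, so sleep overlaps with depression in mediation hypothesis 2.3, and in contrasts 2.2a-2.2d if the PHQ-9 is their outcome

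*Protocol article*

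**What the plan says.** **Primary scale.** Under Measures, Primary Outcomes, Well-being, the article states: "Depressive symptoms are evaluated using the Patient Health Questionnaire-9 (PHQ-9"). It calls the instrument a "self-administered, 9-item questionnaire that assesses each of the 9 DSM-IV depression criteria", with each item scored 0 to 3. No item is omitted from the total.

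**Secondary scale.** Under Secondary Outcomes, Well-being, the BDI-II "is used as a secondary measure of depressive symptom change over time". Its scoring is fixed at item level: "We will sum all items except one sleep item, and the average item score for the remaining 20 items will be multiplied by 21", which keeps the original range.

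**Where each scale is used.** In Primary Analyses, the Aim 2 mixed model behind hypotheses 2.2a-2.2d says: "Depression severity, as assessed by the BDI-II, will be entered as the dependent variable". The same paragraph presents depressive symptoms as the primary well-being measure and lists weeks 0-6, 12 and 28. Hypothesis 2.2b is tested at week 6. Hypothesis 2.3 (mediation) takes the PHQ-9 as dependent variable, calls it the primary outcome measure, and uses each participant's ISI slope over treatment as mediator.

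**Collection schedule.** The opening of Primary Outcomes has the primary well-being outcome at weeks 0, 1-5, 6, 12, 28 and 56. The opening of Secondary Outcomes has secondary measures at weeks 0, 12, 28 and 56, and adds weeks 1-6 only for the secondary insomnia measures and the GAD-7.

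**The concern.** Aim 2 asks whether treating insomnia also improves mental health, and whether improvement in insomnia carries that benefit. All participants enter with a current ISI of at least 10 and the intervention acts on sleep. A depression score that contains a sleep item will therefore respond to treatment, and follow the ISI, even if mood does not change. The BDI-II scoring rule shows that the overlap was recognised, but the rule stops at the secondary scale.

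In hypothesis 2.3 the overlap makes the mediator-outcome association easier to find, and with it the conclusion that insomnia improvement mediates depression improvement. If the PHQ-9 is also the outcome of the arm contrasts, part of the reported depression effect is the insomnia effect counted a second time. The article puts effect sizes ahead of significance tests and offers them to inform later studies, so a bias in the estimate matters more here than a p-value does.

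**Working it through.** **1. The plan's own figure.** Power Calculation gives 80% power with 25 per group, d = 0.80 and a 5% level. Taken as two-sided, the normal approximation gives 80.7% and the exact noncentral t (48 df) 79.1%. The figure reproduces and does not depend on this point. The d of 0.80 serves below only as a yardstick.

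**2. Weight of the sleep item.** The article does not list the PHQ-9 items. That sleep disturbance is one of the nine DSM-IV criteria is common knowledge, not something the text spells out.
- PHQ-9: 3/27 = 11.1% of the maximum, retained.
- BDI-II: 3/63 = 4.8% of the maximum, removed. The rescaled maximum is (20 × 3)/20 × 21 = 63.

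The correction was applied to the scale on which the sleep item weighs less.

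**3. Hypothesis 2.3, where the overlap falls as written.** Write PHQ-9 = S + M, with S the sleep item and M the other eight items. For the ISI slope X:

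Cov(X, PHQ-9) = Cov(X, S) + Cov(X, M)

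The ISI rates early, middle and late insomnia, so the first term is expected to be nonzero by content alone. If M were unrelated to X, the Path B correlation would still be Corr(X, S) × SD(S)/SD(PHQ-9). The article gives none of these quantities, so no figure is put on it.

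**4. Which scale do contrasts 2.2a-2.2d use?**

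| Element of the Aim 2 model | Points to |
|---|---|
| Named dependent variable | BDI-II |
| Described as the primary well-being measure | PHQ-9 |
| Weeks 1-6 in the model, with a test at week 6 | PHQ-9 (BDI-II not listed at those weeks) |
| Weeks 0, 12 and 28 | either |

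On the stated schedule the BDI-II cannot supply the week 6 contrast.

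**5. Size, if the PHQ-9 is the outcome of the contrasts.** Assumed, not from the article: an arm difference on the sleep item of 0.5 to 1.5 points, a PHQ-9 total SD of 4 to 6, and no effect on the other eight items. Added d = sleep-item difference / SD:

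| Sleep-item difference | SD 4 | SD 5 | SD 6 |
|---|---|---|---|
| 0.5 | 0.125 | 0.100 | 0.083 |
| 1.0 | 0.250 | 0.200 | 0.167 |
| 1.5 | 0.375 | 0.300 | 0.250 |

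Against the design effect this is 0.083/0.80 = 10% to 0.375/0.80 = 47%.

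**The case against.** The strongest objection is that the arm contrasts are already free of the sleep item. Primary Analyses names the BDI-II as their dependent variable, and hypotheses 2.2b-2.2d reuse that model. A reader might infer from the PHQ-9's primary status that the main Aim 2 contrasts are contaminated as they stand. The text does not support that: the consequence for 2.2a-2.2d depends on how the conflict over the dependent variable is resolved. This part of the objection stands, and the figures in SD units are conditional on it.

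A reader might also infer that a disagreement between the PHQ-9 and the BDI-II could not be interpreted. That does not follow. A benefit on the PHQ-9 without one on the sleep-free BDI-II would itself suggest overlap, and Secondary Analyses repeats the primary methods on secondary measures. The BDI-II therefore gives a partial check at weeks 12 and 28. It gives none at week 6, which is where the mediation model is spelled out, because it is not listed as collected then.

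Finally, the full PHQ-9 total is the standard score, and a condensed article may leave item scoring to a fuller plan. The first half is fair and is a reason to keep reporting the total. The second half carries less weight, because the article does fix item-level scoring for the other depression scale and gives the reason to do so for this one.

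**Conclusion.** The point holds in limited form. The primary depression scale retains the symptom that the trial treats, while the secondary scale has it removed. As written, the affected analysis is hypothesis 2.3, where Path B is biased towards finding mediation by an amount the article does not allow one to compute. Contrasts 2.2a-2.2d would be affected as well if the PHQ-9 is their intended outcome, which its primary status and the collection schedule suggest but the named dependent variable contradicts. In that case the sleep item alone would add about 0.08 to 0.38 SD in favour of CBT-I, given the assumed item difference and SD. All of this rests on sleep disturbance being one of the nine PHQ-9 criteria. The change should be made, but the trial does not depend on it.

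**What to change.** 1. Reconcile Primary Outcomes, Secondary Outcomes and the Aim 2 paragraph of Primary Analyses, so that one scale is named as dependent variable for 2.2a-2.2d and was collected at every week in the model.
2. Wherever the PHQ-9 is analysed (certainly 2.3, and 2.2a-2.2d if it is the outcome there), apply the rule already written for the BDI-II: drop the sleep item and take the mean of the remaining eight items times 9. The maximum stays 24/8 × 9 = 27. Report the full total alongside, as a sensitivity analysis and to describe severity.

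This costs one derived variable and a short change to the analysis text, with no new data. The article says the primary hypotheses had not yet been tested in full, although a week 6 interim analysis had been run, so the change should be dated relative to that analysis. The downside is that the eight-item score is not the standard total, so comparison with other studies must use the full score, and the reported effect may be somewhat smaller.
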